### Criteria for discontinuing or modifying allocated interventions {11b}

The patient has complications before surgery.The patient agrees to the study but refuses to be randomly assigned.Conditions not suitable for the protocol are found during surgery. For example, during the surgical process, it is found that the patient does not have a suitable free fat flap with ovarian vascular pedicle available, or there is a need to change the surgical method or expand the surgical scope in crisis situations such as bleeding during the operation, or special circumstances with the location, size, and surrounding tissues discovered during the operation.The patient asks to be withdrawn from the protocol.The patient would be unable to continue the protocol due to other postoperative complications.Patients lost to follow-up.

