### Relevant concomitant care permitted or prohibited during the trial {11d}

The similar type of surgery is prohibited during the trialOther complications arising from the procedure can be managed during the trial.Patients who drop out of the experiment during the course of the study will be no longer included in the analyses.Patients with other fatal complications will be no longer included in the analyses.All routine treatment procedures for women in care for low and medium rectal cancer, as deemed appropriate by the patient’s treating clinicians, will be permitted during the trial.Additional clinical review, further treatments, including treatment of rectovaginal fistula, and concomitant medications will be determined by clinical need and will be recorded in follow-up case report forms.

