#### Secondary outcomes

The occurrence time of postoperative RVF.The occurrence time of RVF after stoma closure.Postoperative complications, such as anastomotic leakage, chylous leakage, and intestinal obstruction.Postoperative serological test indexes, such as FSH, LH, E2, CEA, and CA199.Others about evaluating surgical methods, such as the duration of the operation, quality of life, abnormal discharge in the vagina.

The score of a functional assessment of cancer therapy (FACT) system will be used to evaluate the patient’s quality of life.

All data about the outcome will be collected according to the follow-up timepoint in Table 1. Measurement data between the two groups will be analyzed with the *t*-test and rank-sum test, while categorical data will be analyzed with *χ*^2^ test. The duration time will be recorded as mean ± standard deviation, and the incidence data will be recorded as median (first quartile, third quartile). The significance level used for statistical analysis will be two-sided with confidence intervals at the 95% level. All results will be applied to analyze the reliability of the new operation method, and to explore whether this new operation method will cause changes in the related complications, female hormones, affect the effect of the operation, and quality of life.

**Table 1 Tab1:** Schedule of enrolment, intervention, and assessments

Timepoint	Screening	Baseline	Intervention		Follow-up(months)											
			**Before**	**After**	**0**	**3**	**6**	**9**	**12**	**15**	**18**	**21**	**24**	**36**	**48**	**60**

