***Assessments***																
**Primary outcome**																
RVF occurrence						x	x	x	x	x	x	x	x	x	x	x

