**Secondary outcomes**																
The occurrence time of postoperative RVF						x	x	x	x	x	x	x	x	x	x	x
The occurrence time of RVF after stoma closure						x	x	x	x	x	x	x	x	x	x	x
Postoperative complications																
Anastomotic leakage						x	x	x	x	x	x	x	x	x	x	x
Chylous leakage						x	x	x	x	x	x	x	x	x	x	x
Intestinal obstruction						x	x	x	x	x	x	x	x	x	x	x
Postoperative serological test indexes																
FSH		x				x	x	x	x	x	x	x	x	x	x	x
LH		x				x	x	x	x	x	x	x	x	x	x	x
E2		x				x	x	x	x	x	x	x	x	x	x	x
CEA		x				x	x	x	x	x	x	x	x	x	x	x
CA199		x				x	x	x	x	x	x	x	x	x	x	x
The duration of the operation					x											
Abnormal discharge in the vagina						x	x	x	x	x	x	x	x	x	x	x
Quality of life		x				x	x	x	x	x	x	x	x	x	x	x

*RVF* rectovaginal fistula, *FSH* follicle-stimulating hormone, *LH* luteinizing hormone, *E2* estradiol, *CEA* carcinoembryonic antigen, *CA199* carbohydrate antigen199

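### Table 1 schedules no assessment of RVF or surgical complications before month 3, and the exclusion rules can then remove severe early events from the complication comparison

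*Protocol article*

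**What the plan says.** - Outcomes {12} ties collection to the schedule: "All data about the outcome will be collected according to the follow-up timepoint in Table 1".
- The secondary outcomes include "Postoperative complications, such as anastomotic leakage, chylous leakage, and intestinal obstruction", with no time window. The time at which RVF occurs is a separate secondary outcome.
- In Table 1, the rows "RVF occurrence", "Anastomotic leakage", "Chylous leakage" and intestinal obstruction start at month 3. The only outcome marked at month 0 is "The duration of the operation".
- Section {11b} lists this among the reasons for discontinuing: "The patient would be unable to continue the protocol due to other postoperative complications".
- Section {11d} states: "Patients with other fatal complications will be no longer included in the analyses". It also removes anyone who drops out during the study.
- Section {20a} leaves out the data of patients who fall away, and {20c} limits the analysis to cases with no missing data.
- Outside the schedule, {22} has the research team record all adverse events, {11d} puts clinically needed reviews and treatments on follow-up case report forms, and {21b} has complications reported as they occur.

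**The concern.** The experimental operation adds steps to standard surgery: freeing a flap on the ovarian vascular pedicle, dissecting the vessels towards the kidney, and fixing the flap with fibrin glue. Outcomes {12} says the trial will examine whether the new method changes the related complications. The interim plan in {21b} allows the trial to be reconsidered if the experimental arm has more of them. The period soon after the operation is therefore important to the safety comparison, yet the schedule has no outcome assessment there.

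That gap would be minor if every patient reached month 3 and stayed in the analysis. The plan does not ensure this. A patient whose early complication is serious enough to end participation, or is fatal, is the kind of patient the exclusion rules remove. If the two operations differ in severe early complications, the analysed patients may show less of that difference than occurred.

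**Working it through.** The point rests on a schedule and a set of rules. The plan gives no figure to reproduce.

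**Step 1: read the schedule.** Table 1 has 16 timepoint columns: Screening, Baseline, Before, After, and months 0, 3, 6, 9, 12, 15, 18, 21, 24, 36, 48 and 60. Aligning the rows to these columns gives:

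- RVF: 11 marks, at months 3 to 60.
- Anastomotic leakage, chylous leakage and intestinal obstruction: the same 11 marks.
- Duration of the operation: one mark, at month 0.
- The After column: only the two intervention rows.

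So no assessment of these four outcomes is scheduled between surgery and month 3.

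**Step 2: follow a patient with a severe early complication.**

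- If it is fatal, {11d} excludes her directly (the rule refers to other fatal complications).
- If it ends her participation, {11b} lists it as a ground for discontinuation. The intervention is a single operation already performed, so discontinuing at that stage can hardly mean anything but leaving follow-up. She is then a dropout under {11d} and {20a}.
- If she leaves before month 3, all 11 scheduled assessments are missing, so she also fails the complete-case condition in {20c}.

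Her event may well be on file under {22} or {11d}. It is still not in the analysis.

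**Step 3: test whether one change is enough.** If month 0 is marked and the exclusion rules stay, the event is collected on schedule and then removed. If the rules change and month 0 stays blank, the event counts, but only if the event-driven route caught it. Both changes are needed.

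**Step 4: see what can be said about size.** Sample size {14} assumes 20% loss without timing. It gives 115 per group and 144 to be enrolled. Since 115 / (1 − 0.20) = 143.75, 144 is the inflated figure for one group, or 288 for two, although the text can be read as 144 in all. If a share s of the loss falls before month 3 (an assumption), the number leaving by then is 0.20 × s × N:

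| s | N = 144 | N = 288 |
|---|---|---|
| 0% | 0 | 0 |
| 25% | 7 | 14 |
| 50% | 14 | 29 |
| 100% | 29 | 58 |

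These are patients leaving for any reason, not lost events. For scale, removing one patient with an event from an arm of n patients with x events lowers the rate by x/n − (x − 1)/(n − 1) = (n − x)/[n(n − 1)], which is at most 1/n. For n = 115 that is at most 0.87 percentage points. How many such patients there would be, and in which arm, cannot be obtained from the document.

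**The case against.** A reader might infer from Table 1 that the first three months go unobserved, that early events are lost, or that they depend on what unblinded patients remember at month 3. The document does not support any of these.

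- A mark at month 3 is not limited to events present on that day. Because the time of RVF onset is an outcome, the visit has to look back.
- Sections {22}, {11d} and {21b} provide event-driven recording that does not wait for a scheduled visit.
- Section {18a} has separate clinical and patient-reported forms, {19} has raw data collected by assessors blinded to group, and {8} makes this a single-site trial. Nothing makes recall the source for leaks or obstruction.
- An article condenses its protocol. What each form asks, including any look-back to surgery, may be set out in the full forms, which {18a} offers on request.

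All of this stands, and it limits the scheduling gap to a modest one. It is also fair to say that the exclusion rules, not the blank month-0 cells, take early leavers out of the analysis, and that equal under-counting in both arms would not by itself favour either.

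None of it shows that a recorded early event reaches the comparison. The document does not say that adverse-event reports feed the outcome analysis, and it does say that outcome data follow Table 1 and that dropouts and incomplete cases are left out. These are stated rules, not details left to a fuller document.

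**Conclusion.** The point holds in a limited form. The plan schedules no assessment of RVF or the three named complications between surgery and month 3, although it binds outcome data to Table 1 and has a month-0 column available. Early events may be captured by other routes, but the rules for leavers, fatal complications and incomplete cases can take the severe ones out of the complication comparison. The interim comparison may be affected too; that is less certain, because {21b} relies on event-driven reporting and does not say whether the same exclusions apply.

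The size of the bias and the arm it favours cannot be derived. Both depend on when the assumed 20% loss occurs and how much of it is due to complications, and the document states neither. The conclusion rests on two readings: that discontinuing under {11b} after surgery means leaving follow-up, and that the exclusions in {11d}, {20a} and {20c} apply to the complication outcomes as well as to RVF. The text makes no exception for either. The change is worth making because it is cheap and protects the main safety comparison.

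**What to change.** 1. In Table 1, mark month 0 for RVF, anastomotic leakage, chylous leakage and intestinal obstruction. Define month 0 as operation to discharge, with the hospital chart as source, and record the date of each event. State that the month-3 assessment covers everything since discharge.
2. Amend {11d}, {20a} and {20c} so that any event observed before withdrawal or death counts, for every randomised patient, in the arm assigned. Keep all randomised patients in the denominator. Adding back only those leavers who had an event would push the rates upward.
3. Say in {21b} that the interim complication comparison uses the same rule.

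The cost is a little chart abstraction on an existing case report form, with no extra visit or procedure. The change does not settle how to handle patients who leave event-free, whose later outcomes remain unknown; the analysis plan still has to deal with them.

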***Basic information***																
Informed consent	x															
Inclusion/exclusion	x	x														
***Interventions***																
Group A			x	x												
Group B			x	x												
***Assessments***																
**Primary outcome**																
RVF occurrence						x	x	x	x	x	x	x	x	x	x	x
**Secondary outcomes**																
The occurrence time of postoperative RVF						x	x	x	x	x	x	x	x	x	x	x
The occurrence time of RVF after stoma closure						x	x	x	x	x	x	x	x	x	x	x
Postoperative complications																
Anastomotic leakage						x	x	x	x	x	x	x	x	x	x	x
Chylous leakage						x	x	x	x	x	x	x	x	x	x	x
Intestinal obstruction						x	x	x	x	x	x	x	x	x	x	x
Postoperative serological test indexes																
FSH		x				x	x	x	x	x	x	x	x	x	x	x
LH		x				x	x	x	x	x	x	x	x	x	x	x
E2		x				x	x	x	x	x	x	x	x	x	x	x
CEA		x				x	x	x	x	x	x	x	x	x	x	x
CA199		x				x	x	x	x	x	x	x	x	x	x	x
The duration of the operation					x											
Abnormal discharge in the vagina						x	x	x	x	x	x	x	x	x	x	x
Quality of life		x				x	x	x	x	x	x	x	x	x	x	x

*RVF* rectovaginal fistula, *FSH* follicle-stimulating hormone, *LH* luteinizing hormone, *E2* estradiol, *CEA* carcinoembryonic antigen, *CA199* carbohydrate antigen199

### Participant timeline {13}

The timing of intervention and data collection is detailed in Table 1.

### Sample size {14}

Female patients with low and medium rectal cancer in the Department of Colorectal Surgery, Fujian Medical University Union Hospital, from April 2020 to March 2023 are selected as the research participants. It is assumed that the RVF of the study group is the same as that of the control group. According to previous research results and relevant literature reports, the incidence of RVF of the control group and the test group was set at 9.9%, the non-inferior margin value was set at 15%, the test level was set at 0.05, and the power was set at 0.8 [1, 2]. The sample size was calculated by SPSS24.0 software as follows: *N* = 115, and each group needed 115 people. We assume that 20% of patients would be lost to follow-up, and 144 would need to be enrolled.

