### Objectives {7}

In this study, packing the anastomotic stoma with a laparoscopic dislocated fat flap containing ovarian vascular pedicle anterior to the anastomosis to explore whether a statistically significant difference in the incidence of rectovaginal leakage between the experimental group and the control group. Thus, we study the feasibility of this method for the prevention of postoperative rectovaginal fistula, and to provide effective clinical evidence for the prevention of postoperative RVF. The purpose study’s main aim is to evaluate the intervention’s efficacy while analyzing feasibility. The purpose of the study is to evaluate the effectiveness of the intervention methods (preventing rectovaginal fistula) in the experimental group, as well as the feasibility of their clinical implementation and promotion. Finally, we attempt to analyze the population suitable for using this method from the final statistical data.

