### Trial design {8}

This is a single-site parallel group RCT designed to explore the feasibility of packing with laparoscopic dislocated fat flap containing ovarian vascular pedicle anterior to the anastomotic stoma after rectal cancer surgery to prevent RVF. It will be implemented in Fujian Medical University Union Hospital from April 2020 to March 2023. Female patients with low and medium rectal cancer who are eligible will be randomly assigned to the experimental group or the control group in a 1:1 allocation ratio. The sample size should achieve the goal of non-inferiority. All patients will sign the informed consent form before they are enrolled in the trial (Additional file 1).

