## Interventions

### Explanation for the choice of comparators {6b}

This trial will compare the efficacy of preventing RVF. Compared to the control group, the experimental group would add a step to an operation of packing with a dislocated fat flap containing ovarian vascular pedicle anterior. The operations will be performed by the same clinic doctor of the trial at Fujian Medical University Union Hospital. It has the advantages of not being easily perceived by the patient and a higher feasibility of operation.

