#### Group B (control group)

All operations will be performed according to the principle of TME radical resection in rectal cancer surgery.

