### Outcomes {12}

#### The primary outcomes

The primary objective of this trial is to demonstrate the efficacy outcomes of the experimental group in preventing RVF. This includes monitoring the difference in incidence of RVF between the two groups.

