## Statistical methods

### Statistical methods for primary and secondary outcomes {20a}

The independent statistician is responsible for the statistical analysis with SPSS 24.0 software. Patient data that falls off will not be included in the analysis. In the statistical analysis, measurement data between the two groups will be analyzed with the *t*-test and rank-sum test, while categorical data will be analyzed with *χ*^2^ test. Data will be recorded as mean ± standard deviation or median (first quartile, third quartile). The experiment is a non-inferiority trial, and the statistical method is mainly based on “parameter estimation.” Using the primary endpoint, determine the confidence interval for the difference in the efficacy of surgical methods in preventing rectovaginal fistula between the control group and the cases group. The significance level used for statistical analysis will be two-sided with confidence intervals at the 95% level.

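### The trial asks whether the flap prevents RVF but tests non-inferiority to the same surgery without it, with a 15-point margin above the 9.9% control rate

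*Protocol article*

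**What the plan says.** The aim is preventive efficacy. Under the primary outcomes, "The primary objective of this trial is to demonstrate the efficacy outcomes of the experimental group in preventing RVF". Objectives {7} sets out to "explore whether a statistically significant difference in the incidence of rectovaginal leakage between the experimental group and the control group".

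The comparator is the same operation without the flap. Section {6b} says: "Compared to the control group, the experimental group would add a step to an operation". The whole description of Group B is "All operations will be performed according to the principle of TME radical resection in rectal cancer surgery".

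The statistical framework is non-inferiority in three places:
- Trial design {8}: "The sample size should achieve the goal of non-inferiority".
- Sample size {14}: "It is assumed that the RVF of the study group is the same as that of the control group", and "the incidence of RVF of the control group and the test group was set at 9.9%, the non-inferior margin value was set at 15" per cent.
- Statistical methods {20a}: "The experiment is a non-inferiority trial", assessed by a confidence interval for the difference, two-sided at the 95% level.

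No section makes superiority the success criterion, describes a step from non-inferiority to superiority, or sizes the trial for a reduction in RVF.

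**The concern.** Non-inferiority suits a comparison with an active treatment whose benefit is already accepted. Here the control arm has no added preventive step. Being not much worse than omitting the flap is the least one would ask of an extra surgical manoeuvre, and it says nothing about whether the manoeuvre works. The planning assumption makes this plain: the sample size is calculated for a flap that does nothing.

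The margin makes matters worse. It exceeds the assumed control rate and every rate in the 0.9–9.9% range that the protocol cites from the literature. A trial that met its criterion could be reported as evidence of prevention when the flap was ineffective or had raised the RVF rate.

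**Working it through.** **Inputs.** From Sample size {14}: RVF 9.9% in both arms, margin 15%, test level 0.05, power 0.80, 115 per group, 20% loss. From Statistical methods {20a}: two-sided 95% confidence interval. The margin is read as percentage points. Read as 15% of 9.9% (1.485 points), it would need more than 5,000 per arm, so that reading is not plausible.

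**The plan's own figure.** The standard non-inferiority formula is n = 2p(1−p)(z₁₋α + z₀.₈₀)²/margin², with p = 0.099 and margin 0.15.
- One-sided 0.025: 2 × 0.0892 × (1.960 + 0.842)²/0.0225 = 62.2, so 63 per arm.
- One-sided 0.05: 49.0, so 50 per arm.

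The stated 115 per group is not reproduced. The loss step is: 115/0.8 = 143.75, so 144, which follows from the per-group figure. The checks below take 115 evaluable per arm, as the protocol states.

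**What the margin allows.** The limit is 9.9% + 15 points = 24.9%, and 24.9/9.9 = 2.5. The margin is 15/9.9 = 1.52 times the control rate.

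**A result that would pass.** Take 18/115 RVFs with the flap (15.7%) and 11/115 without (9.6%). The difference is +6.09 points with standard error 4.36 points. The 95% interval is 6.09 ± 1.96 × 4.36, or −2.5 to +14.6 points. The upper limit is below 15, so non-inferiority is met although the flap arm has 1.6 times the control rate.

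**Probability of meeting the criterion.** Exact binomial enumeration over all outcomes, control rate 9.9%, success if the upper 95% Wald limit is below 15 points:

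| True RVF rate with flap | 115 per arm | 57 per arm |
|---|---|---|
| 9.9% (no effect) | 96.5% | 77% |
| 15% | 62.9% | 39% |
| 20% | 19.2% | 13% |
| 24.9% (the limit) | 2.8% | 3% |

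The last column covers the reading in which 144 is the total enrolled: 144 × 0.8/2 is about 57 per arm.

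**What the same size offers as a superiority test.** Two-sided 5%, normal approximation: power = Φ{[|p₁−p₂|√n − 1.96√(2p̄(1−p̄))]/√(p₁(1−p₁)+p₂(1−p₂))}. For p₁ = 0.099, p₂ = 0.015, n = 115: (0.901 − 1.96 × 0.328)/0.322 = 0.80, and Φ(0.80) = 0.79. The protocol gives no target rate for the flap arm, so a range is assumed:

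| Assumed RVF rate with flap | Power, 115 per arm | Power, 57 per arm |
|---|---|---|
| 1.0% | 85% | 55% |
| 1.5% | 79% | 49% |
| 2.0% | 72% | 43% |
| 3.0% | 57% | 32% |
| 5.0% | 29% | 17% |

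By exact enumeration, the probability that the 95% Wald interval lies below zero at 115 per arm is slightly higher: 90%, 83%, 76%, 59% and 30%. Halving the rate to 4.95% would need about 440 evaluable per arm for 80% power.

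**The case against.** The best defence is that the plan is less uniformly non-inferiority than it looks. Objectives {7} seeks a significant difference, categorical data are to be compared by χ² test, and the interim section treats the absence of a significant difference as a reason to consider discontinuation. A two-sided 95% interval is planned, and if it fell wholly below zero it would show prevention. The pass rule, upper limit below 15 points, is also not written out; it is inferred from sections {14} and {20a} together. And 24.9% is the boundary of the null hypothesis, not a rate the rule usually lets through: a true rate there passes only about 3% of the time.

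These points are accurate but do not rescue the plan. The inferred rule is the natural reading of a stated margin, a stated trial type and a stated interval. The difference-test language adds a contradiction: at the interim, the equality that the sample size assumes becomes a ground for considering stopping. The interval could support a claim of prevention, but the protocol neither makes that the criterion nor sizes the trial for it.

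Two cautions stand. The size of the problem depends on 115 evaluable per arm; with 57, an ineffective flap passes 77% of the time instead of 97%. And 9.9% is the top of the cited range, so superiority power would be lower with a lower control rate: about 43% for a fall from 5% to 1% at 115 per arm.

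**Conclusion.** The concern holds. The stated objective needs superiority, and the stated test cannot deliver it. On the protocol's own 115 per group, 9.9% control rate and 95% interval, with the margin read as percentage points, an ineffective flap would meet the primary criterion about 97% of the time and one that raised RVF to 15% about 63% of the time. If 144 is the total enrolment, these become 77% and 39%; the mismatch between question and test is the same. This must be corrected before the primary result is analysed.

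**What to change.** Amend Trial design {8}, Sample size {14} and Statistical methods {20a} as follows:
- State a superiority hypothesis: a two-sided 5% test of the RVF risk difference, flap minus no flap, with its 95% confidence interval.
- Claim prevention only if the whole interval lies below zero.
- Remove the 15-point margin from {14} and the non-inferiority statements from {8} and {20a}.
- Replace the sample size justification with what the planned number can detect, for example that 115 evaluable per arm give about 80% power for a fall in RVF from 9.9% to about 1.5%. Say explicitly that 144 is per group.
- Reconcile the interim section, which refers to a significant difference, with the restated hypothesis.

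Keeping non-inferiority with a smaller margin is not a way out at this size. At one-sided 0.025 and 80% power, 115 per arm support a margin of √[2 × 0.0892 × (1.960 + 0.842)²/115] = 11.0 points, still above the control rate. Any non-inferiority statement that is kept must not be reported as prevention.

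The cost is a protocol amendment with ethics and registry resubmission. No extra patients are needed if 144 per group is the plan. The price is candour about power: only a very large reduction is detectable, and a more modest target effect would need a recalculated, larger trial.

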#### Samples

It is expected that the total number of samples would reach 80–100. The cases and controls were grouped according to the experimental protocol, and mid-term experimental data would be collected to analyze the expected risks of intervention measures. When adverse events or other related complications occur, patients who consider adverse outcomes would be reported by the research team and analyzed to determine whether their adverse events are related to the trial, and the research team would fulfill their obligation to inform and respect the patient's right to know related content. In the case of mid-term analysis, if there is no statistically significant difference between the case group and the control group or there are more adverse complications in the case group compared to the control group, the trial can be considered for discontinuation and protocol modification can be carried out. If there are significant modifications during the implementation process, the main researcher shall write and sign a “protocol modification manual” and submit it to the ethics committee for approval before implementation.

In the study, if the analysis results have no clinical significance due to the number of cases, the experimental time will be extended. The interim analysis report will be publicly released by the research participants.

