## Trial status

The trial is approved by the Chinese Clinical Trial Registry(ChiCTR) with trial identifier ChiCTR2000031449, with registration date 26.06.2019, Protocol version 1.0, date: 01.06.2019. All items of the WHO Trial registration data set can be found within the protocol.The trial is approved by the ethical reviewing board of Fujian Medical University Union Hospital(2020YF003-1), date: 02.03.2020. The recruitment for this study started in April 2020 to March 2023. We have recruited 96 people so far. The interventions have also commenced. We are currently at the beginning stages of year 2. Recruitment is expected to be completed at the end of 2023. If there are insufficient recruits during the study period, it is possible to extend the trial period.

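### The stated non-inferiority inputs give about 50 to 75 evaluable patients per group, not 115, and the enrolment figure of 144 is labelled neither per group nor total

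*Protocol article*

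**What the plan says.** All of the inputs stand in the Protocol article, Sample size {14}:

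- Equal true rates: "It is assumed that the RVF of the study group is the same as that of the control group".
- Rates: "the incidence of RVF of the control group and the test group was set at 9.9"%.
- Margin: "the non-inferior margin value was set at 15"%, with no statement of whether this is absolute or relative.
- Level: "the test level was set at 0.05", with no sidedness given.
- Power: 0.8.
- Result: "each group needed 115 people. We assume that 20% of patients would be lost to follow-up, and 144 would need to be enrolled".

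SPSS 24.0 is named as the software, but no formula is given. Trial design {8} sets 1:1 allocation. Statistical methods for primary and secondary outcomes {20a} calls the trial non-inferiority, rests the conclusion on a confidence interval for the difference, and states: "The significance level used for statistical analysis will be two-sided with confidence intervals at the 95% level". The same section leaves dropouts out of the analysis.

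Two other places bear on the target. The interim section says: "It is expected that the total number of samples would reach 80–100". Trial status says: "We have recruited 96 people so far". No enrolled total of 288, and no evaluable total of 230, appears anywhere.

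**The concern.** The section gives every input that a non-inferiority calculation needs, so the result should be reproducible to within a few patients. It is not: 115 is nearly double the standard answer at the analysis level in {20a}. Either an input or the result is misreported, and a reader cannot tell which.

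The last step has a separate problem. The figure of 115 is explicitly per group, while 144 is given only as the number to enrol. The two possible meanings differ by a factor of two, in a trial that is already recruiting. The choice decides how many patients the conclusion rests on, the power, and how far through the trial the interim analysis falls. That last point matters because the interim section allows discontinuation to be considered on the interim result.

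**Working it through.** **Inputs.** p = 0.099 in both groups, true difference 0, margin m = 0.15 (assumed absolute), power 0.80 (z = 0.8416), 1:1 allocation. The level is taken both ways: one-sided 0.05 (z = 1.6449), and one-sided 0.025 (z = 1.9600), which matches a two-sided 95% interval.

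**Step 1: attempt to reproduce 115.** The standard unpooled formula is n per group = (z_α + z_β)² × 2p(1 − p) / m², with 2p(1 − p) = 2 × 0.099 × 0.901 = 0.1784 and m² = 0.0225.

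- One-sided 0.05: 6.183 × 0.1784 / 0.0225 = 49.0, so 50.
- One-sided 0.025: 7.849 × 0.1784 / 0.0225 = 62.2, so 63.

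Other methods and other readings of the margin:

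| Method | One-sided 0.05 | One-sided 0.025 |
|---|---|---|
| Unpooled | 50 | 63 |
| Continuity correction | 62 | 75 |
| Restricted variance (Farrington-Manning) | 58 | 74 |
| Equivalence, two one-sided tests (a different hypothesis) | 68 | 84 |
| 15% read as a ceiling on the rate (margin 0.051) | 425 | 539 |
| 15% read as relative to 9.9% (margin 0.01485) | 5002 | 6350 |

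None gives 115. The nearest match found is 113, from a two-sided superiority comparison of 9.9% with 24.9% with continuity correction. That may be where the figure came from, but it contradicts the stated equal rates and the non-inferiority design, so it does not reproduce the stated calculation.

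Working backwards, 115 per group at 80% power corresponds to a margin of √(0.1784 × 7.849 / 115) = 0.110 at one-sided 0.025, or √(0.1784 × 6.183 / 115) = 0.098 at one-sided 0.05, and not 0.15.

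**Step 2: power at 115 evaluable per group.** SE = √(0.1784 / 115) = 0.03939, and 0.15 / 0.03939 = 3.808.

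- One-sided 0.025: Φ(3.808 − 1.960) = 96.8%.
- One-sided 0.05: Φ(3.808 − 1.645) = 98.5%.

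**Step 3: reproduce 144.** 115 / 0.8 = 143.75, so 144. This is the inflation of one group. For both groups, 230 / 0.8 = 287.5, so 288.

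**Step 4: power if 144 is the total.** 144 / 2 = 72 per arm, and 72 × 0.8 = 57.6, so about 57 evaluable. SE = √(0.1784 / 57) = 0.05594, and 0.15 / 0.05594 = 2.681.

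- One-sided 0.025: Φ(2.681 − 1.960) = 76.5%.
- One-sided 0.05: Φ(2.681 − 1.645) = 85.0%.

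Exact enumeration at 57 per arm gives 76.9% (Wald limits) and 72.8% (Newcombe limits) at one-sided 0.025, and 84.6% and 83.4% at one-sided 0.05. If nobody is lost, 72 per arm gives 85.4% and 91.4% by the normal approximation.

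**Step 5: the interim as a fraction.** 80/288 to 100/288 is 28 to 35%. 80/144 to 100/144 is 56 to 69%.

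**The case against.** The strongest reply is that the trial is not short of power on the natural reading. The clause before 144 speaks of each group, and the arithmetic is per group. Read so, 144 is correctly computed and lacks only a label, and the power exceeds plan. This stands. A reader might infer that 80% power fails on every reading, but the document does not support that. Per group, power is about 97 to 98%. As a total, it falls below 80% only at one-sided 0.025, by about 3.5 points on the normal approximation, and at one-sided 0.05 it is about 85%. Sample size {14} does not state its sidedness, so the shortfall depends on carrying over the interval from {20a}.

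A reader might also infer that 144 was written as the total and that recruitment proves it. The sentence labels the figure neither way, and Trial status cannot settle it. The count of 96 is undated. Spread over the 36 months from April 2020 to March 2023, it is 96/36 = 2.7 per month, or about 120 over the 45 months to the end of 2023, which is nearer 144 than 288. But the same paragraph places the trial early in its second year. If the 96 took about 12 months, the pace is 8 per month, or 288 over 36 months. The paragraph also allows an extension. An interim analysis at 28 to 35% of 288 is early but not unusual.

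Finally, 50 to 63 is specific to the unpooled formula, and no formula is named. This also stands, so the range should run to about 75. It does not rescue 115.

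**Conclusion.** The point holds in two parts.

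1. The figure of 115 per group does not follow from the stated inputs. They give 50 to 63 evaluable per group by the standard formula and up to about 75 by other non-inferiority methods. At 115 the power is about 97 to 98%, not the stated 80%.
2. The figure of 144 is a per-group number without a label. The enrolled total is either 288, with 115 evaluable per group, or 144, with about 57 evaluable per group and power of about 76% (one-sided 0.025) or 85% (one-sided 0.05).

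The finding is an irreproducible figure and an enrolment target uncertain by a factor of two. It does not show that the trial is underpowered, or that 144 is the intended total. The results assume an absolute 15-point margin, equal true rates of 9.9%, 20% loss in each arm and exclusion of those lost. Other readings of the margin move the result further from 115.

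**What to change.** Restate Sample size {14} as one consistent set: rates, margin and its scale, sidedness matching the interval in {20a}, formula, evaluable and enrolled numbers per arm, enrolled total, and the power delivered. Three examples at one-sided 0.025 with the unpooled formula:

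| Evaluable per arm | Enrolled per arm | Enrolled total | Power | Interim at 80 to 100 as a share of the total |
|---|---|---|---|---|
| 63 | 79 (63 / 0.8 = 78.75) | 158 | 80% | 51 to 63% |
| 115 | 144 | 288 | about 97% | 28 to 35% |
| about 57 | 72 | 144 | about 76% | 56 to 69% |

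The sponsor should choose the row that matches what will be recruited. The formula should fit the interval method: with Newcombe limits, exact power at 63 per arm is 77.3%, so the first row would need to be somewhat larger. If an input was misreported, and 115 came from a different margin or test, state the inputs actually used. Express the interim analysis as a fraction of the chosen total.

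The cost is rewriting one paragraph and adding one clause to the interim section. No extra patients are needed if the achievable size and its true power are stated.
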